The incentive scheme ‘starts again’ after birth for two reasons. First, women who have smoked during pregnancy may now wish to become abstinent to avoid affecting their child’s health through environmental tobacco smoke and/or breast milk. For them, this incentive frequency mirrors that during pregnancy for the initial days of a quit attempt. Second, we know that return to smoking after pregnancy is a deliberate choice by many mothers when the incentive to be abstinent due to carrying a baby attached by a placenta is removed. The incentive structure is designed to reward a woman frequently during the initial postpartum period to maintain the incentive to be abstinent when the natural incentive to do so has gone.

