### Study outcomes

#### Smoking cessation: assessed on two occasions

Self-reported, prolonged complete abstinence from smoking (a) between six weeks after enrolment in the scheme and prior to childbirth; and (b) between childbirth and six months later. All women lost to follow-up will be assumed to have resumed smoking. This definition gives women a cessation induction period of up to six weeks, although we expect many women will establish abstinence sooner than this.

These are two outcomes requiring the following different measures:

(a) between six weeks after enrolment in the scheme and prior to childbirth

i. self reported smoking cessation for at least 24 hours at six weeks after enrolment in the scheme, validated by exhaled CO measurement of less than or equal to 6 ppm;

ii. self reported complete abstinence from 6 weeks after enrolment to 36 weeks gestation, validated by salivary cotinine less than 15 ng/ml at 36 weeks. In addition, there must be no reported lapses and a record that all CO readings taken between these dates indicate non-smoking status. All women lost to follow-up will be assumed to have resumed smoking.

(b) between childbirth and six months later

i. self reported smoking cessation for at least 24 hours two days after delivery, validated by exhaled CO measurement of less than or equal to 6 ppm and salivary cotinine less than 15 ng/ml, in keeping with local practice.

ii. self reported complete abstinence from two days after enrolment to six months postpartum, validated by salivary cotinine less than 15 ng/ml at six months. In addition, there must be no reported lapses and a record that all CO readings taken between these dates indicate non-smoking status [27]. All women lost to follow-up will be assumed to have resumed smoking.

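### The six-month postpartum outcome starts its abstinence window two days after enrolment, which contradicts its own heading and first component; most likely a slip for delivery

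*Protocol article*

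**What the plan says.** All the conflicting statements stand in the protocol article under Study outcomes, in the part on smoking cessation assessed on two occasions.

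- The overview gives the second outcome's period as "b) between childbirth and six months later. All women lost to follow-up will be assumed to have resumed smoking".
- The heading of that outcome repeats it: "b) between childbirth and six months later".
- Component (b) i sets the first check at delivery: "self reported smoking cessation for at least 24 hours two days after delivery". An exhaled CO limit and a salivary cotinine limit must both be met at that check.
- Component (b) ii then requires "self reported complete abstinence from two days after enrolment to six months postpartum". A salivary cotinine limit at six months must also be met.
- The next sentence adds that "there must be no reported lapses and a record that all CO readings taken between these dates indicate non-smoking status [27"].

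The same section grants an induction period of up to six weeks. Its pregnancy outcome, (a) ii, accordingly begins six weeks after enrolment and ends at 36 weeks' gestation.

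**The concern.** Component (b) ii is the rule an analyst would code. It fixes the interval over which abstinence must be complete, and the sentence after it makes the same two dates decide which lapses and CO readings disqualify a woman. A wrong start date therefore changes both conditions.

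Taken at its word, (b) ii starts the clock in pregnancy, about six weeks earlier than the pregnancy outcome does. Consider a woman who stops in the third week after enrolment, meets outcome (a) in full and stays abstinent to six months postpartum. She would succeed under the heading of (b) and fail under (b) ii. Two analysts, one following the heading and one following (b) ii, could report different six-month rates from the same data. Abstinence at six months is a named objective and one of the proportions listed under Data analysis.

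**Working it through.** **1. Start points side by side**

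| Place in the protocol article | Start | End |
|---|---|---|
| Overview of outcome (b) | childbirth | six months later |
| Heading of outcome (b) | childbirth | six months later |
| Component (b) i | checked two days after delivery | – |
| Component (b) ii | two days after enrolment | six months postpartum |
| Postpartum saliva samples (Enrolment; Biological samples) | two days after delivery | six months postpartum |
| Component (a) ii, for comparison | six weeks after enrolment | 36 weeks' gestation |

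Only (b) ii places the start of the postpartum outcome before birth. In outcome (a), component ii runs from the time point checked in component i. The same pattern in (b) would start component ii two days after delivery.

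**2. Can enrolment mean something else here?** The Enrolment section describes a single enrolment, at a home visit during pregnancy, and outcome (a) uses the word in that sense. The incentive schedule restarts after birth, but no second enrolment is described.

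**3. Can a woman be expected to be abstinent two days after enrolment?** To be eligible she must report smoking and exceed a urinary cotinine threshold at the enrolment visit. She is encouraged to set a quit date only after consenting, and later telephones to arrange the first visit. No text limits the gap to two days. Since the first scheduled CO visit in Table 2 falls one day after quitting, a woman who sets a later quit date would fail mainly on the self-report requirement.

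**4. Length of the window**

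Inputs: start on the scheme at about 12 weeks' gestation (footnote to Table 2). Assumptions: delivery at 40 weeks, six months = 26 weeks, and 20 and 28 weeks as later enrolment dates.

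As written: (40 − g) × 7 + 26 × 7 − 2 days, where g is gestation at enrolment in weeks. From two days after delivery: 26 × 7 − 2 = 180 days.

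| g (weeks) | As written (days) | From two days after delivery (days) | Ratio |
|---|---|---|---|
| 12 | 196 + 182 − 2 = 376 | 180 | 2.1 |
| 20 | 140 + 182 − 2 = 320 | 180 | 1.8 |
| 28 | 84 + 182 − 2 = 264 | 180 | 1.5 |

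If the last scheduled visit, 28 weeks after delivery in Table 2, is used as the end point, the 12-week figures become 196 + 196 − 2 = 390 and 196 − 2 = 194 days, a ratio of 2.0.

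**5. The plan's own figures**

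The Precision estimation section gives half-widths of 4% and 7%. With 1.96 × √(p(1 − p)/n):

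- n = 500, p = 0.30: 4.02%
- n = 150, p = 0.24: 6.83%

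Both are reproduced. Neither depends on the start point of (b) ii, so the correction leaves them unchanged.

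**The case against.** The strongest reply is that no careful analyst would be misled. The period is stated twice as beginning at childbirth, (b) i and the sampling schedule agree, and one word stands against all of them. The outcome is also secondary: the two primary outcomes are cessation at delivery and false reporting to gain an incentive. This stands, and it limits the weight of the point. It does not make the definition usable as written, because (b) ii is the detailed rule and the heading only its title.

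Several stronger readings are tempting, and the document does not support them.

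- **That the study measures a different, far stricter endpoint, so its six-month rate will be biased downward.** This holds only if the analysis follows the single word against the surrounding text. Nothing shows that it will.
- **That the loss can be put at 6 to 18 percentage points.** A reader might take the 36 forecast quitters (24% of 150), suppose that 25–75% of them stopped after day two, and count 9 to 27 women. That share has no source in the document, and the count treats all 36 as six-month successes. The Background puts relapse in the six months after delivery at 70%. Applied here, that leaves 36 × 0.30 ≈ 11 women, of whom the same share is about 3 to 8, or 2 to 5 points of 150. That lower range still rests on the unsourced share, so neither range is an estimate.
- **That the slip alone shuts out women who first stop around birth.** The section on the incentive scheme says that "women who have smoked during pregnancy may now wish to become abstinent to avoid affecting their child"'s health, and the literal (b) ii would fail them. But (b) i also requires low salivary cotinine two days after delivery, and the protocol says cotinine reflects the preceding few days. Some of these women may fail (b) i whatever (b) ii says.
- **That the wording conflicts with the stated objective.** Objective 2(b) asks for prolonged abstinence at six months postpartum and sets no start point. The conflict is within the outcome section.

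**Conclusion.** The inconsistency is real: (b) ii contradicts the overview and heading of its own outcome, component (b) i and the postpartum sampling times. It is most likely a drafting slip in a secondary outcome. Read literally, it makes the required window about 2.1 times as long for a woman enrolling at 12 weeks and about 1.5 times for one enrolling at 28 weeks. These ratios rest on delivery at 40 weeks and six months of 26 weeks. It also cancels the induction period and fails women who quit more than two days after enrolment and then remain abstinent throughout. How far this would move the six-month rate depends on when women stop relative to enrolment, which the document does not report. The primary outcomes and the precision figures are unaffected.

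**What to change.** In component (b) ii, replace enrolment with delivery, so that complete abstinence runs from two days after delivery to six months postpartum. The next sentence needs no change: its condition on lapses and CO readings already refers to the two dates and will then cover the intended window.

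The cost is one word, plus a check that any analysis code uses the delivery date as the start. No extra data, visits or samples are needed. The correction should be recorded before the six-month data are analysed, so that the choice of definition cannot depend on the results.

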##### Other measures of smoking status

Self reported prolonged abstinence from smoking assessed by self-reported smoking cessation six weeks after enrolment in the scheme, validated by CO reading, and self report smoking cessation at 28 weeks gestation, validated by salivary cotinine less than 15 ng/ml.

##### Participation in the scheme

This will be recorded by the study support worker and presented as a proportion of all women routinely recorded at booking consultations as smoking.

##### Predictors of smoking cessation

Women will complete a questionnaire when they are recruited to the scheme to assess the following: delay discounting for self and the baby, using an adapted version of Kirby and Marakovic’s task [16]; nicotine addiction, using the Fagerstrom test for nicotine dependence [30]; and, socio-economic status, assessed using postcode as an index of area level deprivation.

#### Estimating the adverse effects of using incentives to achieve quitting

a) *delay in quitting smoking to enrol in an incentive scheme*: There are concerns that the estimated 11% of women who quit smoking upon learning they are pregnant may delay quitting until they can enrol in the incentive scheme. We will estimate this effect by comparing the self-reported smoking status of women during the time the scheme is running, with that recorded for the preceding 12 months. While this is open to the usual biases associated with historic controls, it will provide some indication of whether the scheme has delayed quitting.

b) *gaming i.e. false reporting of smoking status:* Two types of gaming are possible;

i) *To gain entry to the scheme (i.e. non-smokers acting as smokers).* We will estimate this in two ways: first, using historic controls (by comparing the proportion of women who claim to smoke at the outset of the study with the proportion who reported being smokers in the year prior to the start of the scheme); second, by assessing the proportion of women claiming to smoke with levels of urinary cotinine compatible with non-smoker status. Our inclusion criteria are set to minimise entry to the scheme by non-smokers.

ii) *To gain an incentive (i.e. smokers acting as non-smokers).* We will estimate this by validating CO records and self-reported smoking status against measurement of cotinine collected at 28 weeks gestation, 36 weeks gestation and 2 days after delivery and 6 months post-partum.

The two primary outcomes of this study are:

smoking cessation at delivery; and,

false reporting of smoking status to gain an incentive.

The remaining outcomes will be considered secondary.

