### Recruitment and screening

Midwives currently record the smoking status of all women they book for antenatal care. All women reporting to a midwife at booking that they smoke occasionally or every day will be referred to the Derbyshire Community Healthcare Service (DCHS) Stop Smoking Service (SSS) as is current standard care. Forms describing the smoking status of all women being booked during the pilot period will be posted first class to the SSS. The midwife will give women who smoke two leaflets: one that outlines the incentive scheme and one outlining the stop smoking services.

Women who smoke will be phoned by a support worker from the SSS within one working day of receipt of their referral from the midwife. The support on offer will be described, namely stop smoking services and the financial incentive scheme. Women will be informed that the latter is for heavier smokers with joining dependent upon a urinary cotinine concentration above a certain level (at least 1.5 mg/ml).

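### The estimate of delayed quitting is confounded with false entry: its only estimator is in substance also the first estimator of false entry

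*Protocol article*

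**What the plan says.** Objective 4 (Study aim and objectives) lists delay in quitting and false reporting to gain entry as separate adverse effects. The methods are in the section Estimating the adverse effects of using incentives to achieve quitting.

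- **Delay, item (a).** The worry is that "the estimated 11% of women who quit smoking upon learning they are pregnant may delay quitting" until they can enrol. The only method given is "comparing the self-reported smoking status of women during the time the scheme is running, with that recorded for the preceding 12 months". The protocol concedes that historical controls bring bias and claims no more than an indication.
- **False entry, item (b)(i).** "We will estimate this in two ways": first, "by comparing the proportion of women who claim to smoke at the outset of the study with the proportion who reported being smokers", with the pre-scheme year as the reference; second, "by assessing the proportion of women claiming to smoke with levels of urinary cotinine compatible with non-smoker status".

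Urine is tested at the enrolment visit, which is arranged for women who want to be considered for the scheme (Enrolment). Before that, by telephone, "Women will be informed that the latter is for heavier smokers with joining dependent upon a urinary cotinine concentration above a certain level" (Recruitment and screening).

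Data analysis promises proportions with 95% confidence intervals and no formal tests. False entry is in its list of reported proportions; delay is not. The same adverse-effects section makes both outcomes secondary.

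**The concern.** A woman who postpones quitting until she can enrol is a true smoker at booking who, without the scheme, would not have been one. A false entrant is a non-smoker who says she smokes. Both raise self-reported smoking at booking relative to the prior year. For delay, that difference is all the protocol has.

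The stated caveat covers changes over time and comparability of the two years. It does not warn that the same rise is also put forward as evidence of gaming. A reader shown a rise under delay could take it as harm from postponed quitting when some or all of it is false claiming; a background fall in smoking could hide either.

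The Background says no previous study has examined delay, so this estimate may be relied on when incentive schemes are designed.

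**Working it through.** **Inputs.** 2,881 women in the historical year and 500 smokers at booking, given as 17% (Public attitudes); 500/2881 = 17.4%. Expected enrolment is 30% of 500 = 150 (Precision estimation). The 11% has no explicit denominator. Assumption: the scheme year also has 2,881 women.

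**1. The protocol's own precision figures.** Half-width = 1.96 × √(p(1−p)/n).
- 30% of 500: 4.02 points (stated 4).
- 24% of 150: 6.83 points (stated 7).

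Both reproduce. No figure is given for delay or false entry.

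**2. What the before/after difference contains.** Change in self-reported smoking = delay + false entry + secular change: one observed quantity, three unknowns. Item (a) refers to the time the scheme is running and (b)(i) to the outset of the study, but both set self-reported smoking under the scheme against the prior year.

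Illustration with no secular change: a 2-point rise, from 17.4% to 19.4%, is 0.02 × 2881 ≈ 58 extra self-reported smokers. Splits of 58 delayed and 0 false, 29 and 29, or 0 and 58 all give 19.4%.

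**3. Precision of the difference.** Half-width = 1.96 × √(2p(1−p)/2881).
- p = 0.17: 1.96 × √(2 × 0.17 × 0.83/2881) = 0.0194, or 1.94 points.
- p = 500/2881: 1.96 points, about 56 women.

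This is the uncertainty of the combined change.

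**4. How large delay could be.** If every woman in the 11% delayed:
- 11% of pre-pregnancy smokers: 0.17/0.89 = 0.191, a rise of 2.1 points, close to the half-width.
- 11% of all women: 17% + 11% = 28%, a rise of 11 points, more than five times the half-width.

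**5. What cotinine adds.** A woman who delays should test as a smoker; a false entrant should not. Suppose, in the 2-point illustration, all 558 self-reported smokers were tested. Non-smoker fractions of 0%, 5% and 10% would attribute 0, 28 and 56 women to false entry, leaving about 58, 30 and 2 for delay. So full testing could separate the two, if secular change were nil.

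Testing will not be full. Women who report smoking at booking but do not take up an enrolment visit count in the before/after difference and give no urine. The number tested is not stated; taking 150 to 500 as an assumed range:

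| Women tested | Half-width at 5% | Half-width at 10% |
|---|---|---|
| 150 | 3.5 points | 4.8 points |
| 500 | 1.9 points | 2.6 points |

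Women are also told of the threshold beforehand, which may keep false claimants from being tested. The fraction among women tested therefore cannot simply be applied to all self-reported smokers and subtracted.

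**The case against.** The strongest reply is that the protocol already separates the two effects. The cotinine estimate of false entry does not use the prior year, and it distinguishes a true smoker from a non-smoker. This stands: a reader might infer that neither harm can be told from the other, and the documents do not support that. The confounding falls on delay; false entry has its own estimate, though a partial one.

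Three other strong readings also fail.

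- **That one rise will be counted in full as two harms.** The text does not say so. It offers the comparison only as an indication for delay, and Data analysis reports false entry as a proportion of women, which fits the cotinine measure.
- **That truthful light smokers will be labelled as cheating.** The only urinary cut-off given is the eligibility level, and midwives also refer occasional smokers, so the risk exists. But item (b)(i) speaks of levels compatible with not smoking and does not say the eligibility level will serve for that. An article may leave the exact cut-off to a fuller document.
- **That the study cannot detect even complete delay.** This depends on what the 11% is a share of; under one reading the effect would be plainly visible.

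It is also fair that the protocol admits historical-control bias and, in its Discussion, the lack of a comparison group. Neither statement mentions that delay and false entry push the same figure in the same direction.

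**Conclusion.** The point holds for delay. Its only estimator is shared in substance with false entry and also absorbs secular change; the protocol neither says so nor says that the cotinine result will inform the delay estimate. This does not depend on sample size or on the reading of the 11%.

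The size does depend on assumptions. With equal years of 2,881 women, the half-width of about 1.9 points compares with a ceiling for delay of 2.1 or 11 points.

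Consequences are moderate. Both outcomes are secondary. Cessation at delivery and false reporting to gain an incentive, the two primary outcomes, do not use this comparison. The change is still worth making, because delay and false entry are named objectives and appear among the main results in the abstract.

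**What to change.** 1. Report the before/after change in self-reported smoking at booking once, with a 95% confidence interval for the difference, as the combined effect of delay, false entry and secular change. Do not present it as an estimate of either harm alone.
2. Base false entry on urinary cotinine, with women tested as the denominator. Report three classes: non-smoker level, above that but below the eligibility level, and eligible. State how many self-reported smokers were not tested.
3. Add one item to the recruitment questionnaire or the planned telephone interviews: when the woman first heard of the scheme and whether she put off quitting because of it.
4. Show the trend in smoking at booking from several earlier years of the same routine data.

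The cost is some wording, one question and a data extract. The delay item is self-reported and reaches only recruited women, expected to be about 30% of smokers. It misses women who delayed and did not join, so it supplements the population comparison and does not replace it.

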The Cessation in Pregnancy Incentives Trial (CPIT)	Greater Glasgow and Clyde	Active	UK	Chief Scientist Office Scottish Government (sponsored by the NHS)	Up to £400 in shopping vouchers for abstinence up to 34 to 38 weeks gestation	CO testing and urine test (for final payment)	http://www.controlled-trials.com/ISRCTN87508788/ - Accessed 19 November 2012
							Trial protocol available at http://www.trialsjournal.com/content/13/1/113 Accessed 19 November 2012
HERS (Health Enhancement Reward scheme)	West Suffolk (Bury St Edmunds and Sudbury)	Completed	UK	NHS	Up to £120 in vouchers (£10 per month) for baby products, beauty treatments and cinema tickets.	CO testing	Health Enhancement Reward Scheme (HERS) Project Evaluation - UCS Full Report January 2010
							http://www.suffolk.nhs.uk/Home/Publications/20092010.aspx Accessed 19 November 2012

From information available on websites and from our knowledge of financial incentives schemes currently running in the UK, only one is part of a randomised trial (the Cessation in Pregnancy and Incentives Trial [21]). The current study differs from this trial by using a more frequent incentive schedule (a maximum of 32 incentive points compared with four), offered for longer (up to six months postpartum compared with 36 weeks gestation), and in which the size of incentives is incremental, as opposed to fixed. The incentive schedule for the current study (see Table 2) is based on those used in two USA studies which reported large effect sizes [13,14].

**Table 2 T2:** **Incentive schedule**^**1**^

**Visit no.**	**Visit timepoint**	**Incentive (£)**	**Cumulative total (£)**
1	1 day after quitting	8	8
2	3 days after quitting	8 + 1	17
3	7 days after quitting	9 + 1	27
4	12 days after quitting	10 + 1	38
5	3 weeks after quitting	11 + 1	50
6	4 weeks after quitting	12 + 1	63
7	5 weeks after quitting	13 + 1	77
8	6 weeks after quitting	14 + 1	92
9	8 weeks after quitting	15 + 1	108
10	10 weeks after quitting	16 + 1	125
11	12 weeks after quitting	17 + 1	143
12	14 weeks after quitting	18 + 1	162
13	16 weeks after quitting	19 + 1	182
14	20 weeks after quitting	20 + 1	203
15	24 weeks after quitting	21 + 1	225
16	28 weeks after quitting	22 + 1	248
DELIVERY			
17	2 day after delivery	23 + 1	272
18	4 days after delivery	24 + 1	297
19	7 days after delivery	25 + 1	323
20	12 days after delivery	26 + 1	350
21	3 weeks after delivery	27 + 1	378
22	4 weeks after delivery	28 + 1	407
23	5 weeks after delivery	29 + 1	437

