### Measuring smoking cessation

To assess the effectiveness of the intervention it is necessary to have an accurate measure of smoking cessation. For most people who smoke cigarettes and have difficulty quitting (addicted smokers), only the state of complete abstinence is sustainable as occasional smoking leads to reinstatement of fulltime smoking. The outcome of choice for smoking cessation studies should therefore be prolonged or continuous abstinence [27,28]. In particular, this is the only outcome known to be associated with health benefits.

Biochemical verification tests, such as testing CO levels or nicotine metabolites such as cotinine, are the preferred methods of validating smoking cessation in clinical studies such as this [29]. Testing for CO levels using a breath test assesses smoking in the preceding one to four hours whereas cotinine analysis from blood, urine or saliva samples can measure exposure to smoking in the preceding few days [29]. However, testing for cotinine in body fluids is more complex to administer and expensive to analyse than testing CO levels.

In the current study we will use cotinine from urine samples to confirm smoking status at recruitment, and from saliva samples to verify abstinence both at delivery and at six months post-partum. Cotinine testing will also be used once during pregnancy (at around 28 weeks) to compare with CO measurements taken at the same time. For practical reasons, CO tests alone will be used on all other occasions when women attend to receive incentive payments.

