### Biological samples taken to assess quitting and gaming

A urine sample is tested at the enrolment visit, using a dipstick test, to assess eligibility for the scheme, with urinary cotinine concentrations equal to or more than 1.5 mg/ml sufficient for enrolment.

Saliva samples are collected by the support worker at 28 weeks gestation, 36 weeks gestation, 2 days post delivery and amongst women reporting cessation, at 6 months post delivery and analysed by a nationally accredited laboratory for cotinine concentrations. For women reporting current use of nicotine replacement therapy, anabasine, a tobacco specific alkaloid, will be analysed.

In addition to being used to biochemically verify quitting, the results of these analyses will be used to estimate the proportions of women reporting having quit who have not. Both women and the support worker will remain blinded to the test results unless a woman requests her result. Women proven to be smoking on any of these extra tests (i.e. those using saliva as opposed to CO) will not be confronted with this, withdrawn from the scheme or refused vouchers. The aim is to estimate the extent of the gaming that is occurring. It is possible for women to abstain for a few hours and pass a CO test but such women would be shown to be smokers by salivary cotinine.

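### At the sample taken two days after delivery, the false-reporting primary outcome can count a woman who truthfully stopped at delivery as a false reporter

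*Protocol article*

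**What the plan says.** - **Outcome.** The section on estimating adverse effects lists "false reporting of smoking status to gain an incentive" as one of two primary outcomes.
- **Measurement.** The same section, item (b) ii, says: "We will estimate this by validating CO records and self-reported smoking status against measurement of cotinine collected at 28 weeks gestation, 36 weeks gestation". It goes on to name two further samples, two days after delivery and six months post-partum.
- **Reading of a positive result.** Under Biological samples taken to assess quitting and gaming, the results serve to "estimate the proportions of women reporting having quit who have not". The text speaks there of "Women proven to be smoking on any of these extra tests", meaning the saliva tests. No minimum time since stopping is attached.
- **Assay windows.** Measuring smoking cessation gives breath CO a window of one to four hours, and says of cotinine that it "can measure exposure to smoking in the preceding few days". No decay time is given.
- **Schedule.** In Table 2 the first paid visit of a pregnancy attempt is "1 day after quitting". The first paid visit after birth (visit 17) is on day 2, the same day as a saliva sample.
- **Restart at birth.** The incentive scheme section says the scheme begins afresh after delivery, partly for women who smoked in pregnancy and now want to stop. For them, "this incentive frequency mirrors that during pregnancy for the initial days of a quit attempt".
- **What is declared.** Three sections differ. The incentive scheme section requires complete abstinence since the previous contact. Study outcomes (b) i asks, two days after delivery, for at least 24 hours without smoking. The Visits section requires only that the woman says she is not smoking and has a low CO reading.

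**The concern.** A negative CO with a positive cotinine fits two different women. One abstained for a few hours to pass the breath test. The other really stopped a day or two ago and still carries cotinine from before. The section on biological samples discusses only the first. Two days after delivery the second woman is someone the scheme expressly hopes to attract, so following the stated rule can score her as gaming for doing what the restart invites.

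The error runs in one direction: it raises apparent false reporting. The Discussion puts weight on this result, since it promises rigorous gaming data with implications for how earlier incentive studies are read. The women themselves lose nothing, because a positive saliva test does not stop their vouchers. What is at stake is the published estimate.

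**Working it through.** **1. The plan's own figures.** Precision estimation gives half-widths of 4% and 7%. With 1.96·√(p(1−p)/n):
- 30% of 500: 1.96·√(0.30·0.70/500) = 4.02%.
- 24% of 150: 1.96·√(0.24·0.76/150) = 6.83%.

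Both reproduce. No expected rate or precision is stated for false reporting. The expected number of quitters is 0.24 × 150 = 36.

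**2. Time since stopping at each cotinine sample** (from Table 2)
- *28 and 36 weeks.* Quitting at 12 weeks gives (28−12)×7 = 112 and (36−12)×7 = 168 days. Quitting at 24 weeks gives 28 and 84 days. All lie well outside a window of a few days. Only a woman who began or restarted within days of the sample is exposed.
- *Six months.* Scheduled visits are 28 days apart by then, so exposure needs a very recent renewed attempt.
- *Two days after delivery.* A woman who stopped at birth has at most 2 days of abstinence. That lies inside the stated window and satisfies the 24-hour question.

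**3. Would she test positive?** The documents do not say. As an assumption, take the 15 ng/ml saliva cut-off from Study outcomes, starting levels of 50 to 300 ng/ml and half-lives of 9 to 24 hours. The level after two days is start × 0.5^(48/half-life):
- 50 ng/ml, 24 h: 12.5 (negative)
- 300 ng/ml, 9 h: 7.4 (negative)
- 100 ng/ml, 24 h: 25 (positive)
- 300 ng/ml, 17 h: 42.4 (positive)

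Some truthful new quitters would pass and some would not.

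**4. Size, by illustration only.** Suppose that on day 2 there are 36 longer-standing claims, 4 of them false (the 4 is assumed). Add x women who stopped at delivery and are all still positive. Apparent rate = (4+x)/(36+x); true rate = 4/(36+x).

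| x | apparent | true |
|---|---|---|
| 0 | 4/36 = 11% | 11% |
| 1 | 5/37 = 14% | 4/37 = 11% |
| 5 | 9/41 = 22% | 4/41 = 10% |
| 10 | 14/46 = 30% | 4/46 = 9% |
| 15 | 19/51 = 37% | 4/51 = 8% |

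This is an upper bound for each x, because every added woman is taken as positive.

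**5. Less extreme values.** Let f be the false-report rate among the other claimants, q the share of claimants truthfully in their first days, and s the share of those still positive. Apparent = f(1−q) + s·q; true = f(1−q). With f = 10% and s from 0.5 to 1:
- q = 2%: true 9.8%, apparent 10.8 to 11.8%
- q = 5%: true 9.5%, apparent 12.0 to 14.5%
- q = 20%: true 8.0%, apparent 18.0 to 28.0%

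At q = 0 there is no bias. The documents supply neither q nor s.

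**The case against.** **A woman must declare abstinence since the last contact.** Mid-schedule, visits are mostly two to four weeks apart. A woman who stopped only days before a 28-week, 36-week or six-month sample could not truthfully make that declaration, so a positive cotinine would rightly mark a false report. This stands for most such women, though not for one starting a first attempt. On day 2 it is weaker. Read strictly, it would also bar a woman who stopped at delivery, which sits badly with the stated reason for the restart. The 24-hour question and the Visits procedure both let her answer truthfully. The documents do not settle which declaration counts.

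**Saliva is taken at four fixed times, not at the day-1 and day-3 visits.** This stands. The early vouchers alone do not create the problem.

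**Few women may be affected.** This also stands as an unknown. Enrolment follows antenatal booking, so the group consists only of women already enrolled, still in contact and newly stopping at birth. No number is given for them.

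**A fuller plan may handle recent quits.** It may. But the article does more than stay silent: it states how a positive result is read, for a primary outcome. Quit dates anchor the pregnancy visits, but visits after birth are timed from delivery, so a stop date at birth is not captured by the schedule itself.

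**A stronger reading.** A reader might infer that anyone who stopped one to three days earlier is scored as false at all four samples. The documents do not support this. They give no decay time, and the first three answers above narrow the reach.

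**Conclusion.** The point holds for the sample two days after delivery. There the restart, the paid visit, the 24-hour question and the saliva test coincide, and the stated reading of a positive cotinine makes no allowance for a woman who stopped at birth. It rests on two assumptions: that some enrolled women do stop at delivery, and that some of them are still above the cut-off two days later. Both are plausible on the text, but neither is quantified there.

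At the other three samples the effect is confined to women in the first days of an attempt and is probably slight. The bias in the primary outcome can range from nil to large. The 22%, 30% and 37% figures are an assumed upper bound for day 2, not estimates, and should not be read as the effect on the outcome across all four samples. The flaw is worth correcting because it always inflates a primary result and costs little to mend.

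**What to change.** In the section on estimating adverse effects, item (b) ii, and in the section on biological samples:

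1. Record the claimed date of the last cigarette at each cotinine sample, and fix the assay look-back in advance with the laboratory.
2. Report the day-2 sample separately from the other three.
3. Give two figures for false reporting: one counting cotinine-positive women whose claimed stop falls inside the look-back as false reporters, one not, with their number. Keep them in the denominator of both, so that the figures bound the rate. In the illustration with x = 5 these are 9/41 = 22% and 4/41 = 10%. Dropping the women from the denominator as well would give 4/36 = 11%, above the true value.
4. Reconcile the incentive scheme, Study outcomes and Visits sections on what period of abstinence a woman declares, and define a false report against that declaration.

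The cost is one extra date item and a range instead of a single figure at day 2. The lower figure may understate gaming, because the date is itself self-reported and a false reporter could claim a recent stop. For that reason both figures are needed, and simple exclusion is not enough.
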